### Participating Sites

Participating sites are responsible for performing the following tasks:

- Following the protocol as written, and the guidelines of Good Clinical Practice (GCP).
- Submitting data to the Coordinating Center.
- Registering all patients with the Coordinating Center by submitting patient registration form, and signed informed consent promptly.
- Providing sufficient experienced clinical and administrative staff and adequate facilities and equipment to conduct a collaborative trial according to the protocol.
- Maintaining regulatory binders on site and providing copies of all required documents to the Coordinating Center.
- Collecting and submitting data according to the schedule specified by the protocol.

## **12.2 Safety Meetings**

Scheduled meetings will take place bi-weekly and will include the protocol principal investigator, study coordinator(s), data manager(s), sub-investigators (as appropriate), collaborators (as appropriate), and biostatisticians (as appropriate) involved with the conduct of the protocol. During these meetings matters related to the following will be discussed: safety of protocol participants, validity and integrity of the data, enrollment rate relative to expectation, characteristics of participants, retention of participants, adherence to protocol (potential or real protocol violations), data completeness, and progress of data for objectives.

Teleconferences will be scheduled to include the Investigator and/or representatives from each site based on patient enrollment. During these meetings, the Investigators will discuss progress updates with a focus on safety of the protocol participants, enrollment status, and progress of data for objectives.

## **12.3 Monitoring**

This is a DSMP Level II study under the SKCCC Data Safety Monitoring Plan (DSMP, 12/6/2012). Eligibility for all sites will be monitored by the Protocol chair. Data monitoring of this protocol will occur on a regular basis with the frequency dependent on the rate of subject accrual and the progress of the study. The protocol will be monitored internally by the Principal Investigator at each site. Additional data and safety monitoring oversight will also be performed by the SKCCC Safety Monitoring Committee (SMC - as defined in the DSMP). External monitoring will occur according to the following guidelines:

Johns Hopkins SKCCC: The protocol will be monitored externally by the SKCCC CRO in accordance with SKCCC guidelines. Trial monitoring and reporting will be done through the Compliance Monitoring Office at SKCCC.

Participating site(s): The protocol will be monitored by the internal CRO at each site. A report of the reviews will be submitted to the Johns Hopkins principal investigator and SKCCC CRO.

Authorized representatives of the Coordinating Center may visit the satellite sites to perform audits or inspections, including source data verification. The purpose of these audits or inspections is to systematically and independently examine all trial-related activities and documents to determine whether these activities were conducted and data were recorded, analyzed, and accurately reported according to the protocol, Good Clinical Practice (GCP), and any applicable regulatory requirements.

## **13. STATISTICAL CONSIDERATIONS**

### **13.1 Study Design/Endpoints**

This phase I study will evaluate up to 8 dose levels of Helixor® M as a single agent to determine the MTD of Helixor® M in patients with advanced solid tumors. The Helixor® M study dose levels are 150 mg, 300 mg, 600 mg, 900 mg, 1200 mg, 1500 mg, 1800 mg,

and 2000 mg. Patients will be assigned to a dose level in the order of study entry. If MTDs are not determined at the dose of 2000 mg, this will be the dose taken to the expansion phase and no further escalation of dose is planned.

An accelerated titration design (ATD) will be utilized to determine the MTD. The first cohort of 1 subject will receive Helixor® M at the 150mg dose level. One subject will be enrolled in each cohort until a subject experiences a grade 2 or higher drug related toxicity, whereupon an additional 2 patients will be enrolled at that dose level. Patients will be observed for DLTs through the first three doses at the highest dose per dose level (i.e. 150 mg for DL1, 300 mg for DL2, 600 mg for DL3, etc.). Thereafter, the study will become the traditional 3 + 3 design with 3 or 6 patients treated at this dose level and at all subsequent dose levels depending upon the incidence of DLTs.

If no DLTs occur in a cohort of 3 patients, a new cohort of 3 patients will be treated at the next higher dose level. If 1 of 3 patients in a cohort experiences a DLT, that cohort will be expanded to 6 patients. If only 1 of the 6 patients experiences a DLT, then the next cohort of 3 patients will be treated at the next higher dose level. If 2 or more DLTs occur within a cohort, then that dose level will be above the maximum tolerated dose, and new patients will be enrolled at the previous lower (tolerated) dose level until that cohort has 6 patients. A total of 6 patients must be enrolled at a dose level in order to declare MTD. If  $\leq 1$  in 6 patients experience DLT at a dose level, dose escalation will stop and this dose level will be the recommended dose for the expansion phase.

The target DLT rate is  $< 33\%$ . The MTD will be defined as the dose of Helixor® M in which  $< 2$  of 6 patients experiences a dose limiting toxicity (DLT) with the next higher dose having at least 2 of 3 or 2 of up to 6 patients experiencing a DLT. A subject who is withdrawn from the study prior to completion of the DLT period for a reason other than a DLT and has not experienced a study drug-related adverse event of  $\geq$  grade 2 may be replaced.

Once the MTD (or maximum administered dose if no MTD is determined) has been defined, an additional 10 patients will be enrolled and treated at that dose level in an expansion phase (for a total of 16 patients treated with the MTD) to further characterize safety and obtain preliminary estimates of efficacy.

Continuous evaluation of toxicity events in the expansion cohort will be performed throughout enrollment. If the rate of toxicities meeting DLT criteria appears to be higher than 30%, we will temporarily halt the study pending dose modification. Specifically, we will apply a Bayesian toxicity monitoring rule that suspends the enrollment if the posterior probability of risk being larger than 0.3 is 75% or higher.

We expect the SAE rate is about 27%. The monitoring rule uses  $\text{beta}(2, 5.5)$  as a prior distribution. This means that our prior guess at the proportion of toxicity is 27%, and there is 90% probability that this proportion is between 6% and 55%.

The decision rule for safety stopping is as follows:  
Stop if:

|        |   |   |   |    |
|--------|---|---|---|----|
| # AE   | 2 | 3 | 4 | 5  |
| Out of | 2 | 3 | 6 | 9  |
|        |   | 4 | 7 | 10 |
|        |   | 5 | 8 |    |

For example, if two out of the first 2 patients have adverse events, we will stop the accrual. If three or more out of the first 3-5 patients have adverse events, we will stop.

The operating characteristics of the stopping rule are shown below and are based on 5000 simulations:

| True AE rate | % Simulated trials declaring unsafe | Average sample size (out of 10) |
|--------------|-------------------------------------|---------------------------------|
| 0.10         | 5.1                                 | 9.7                             |
| 0.20         | 10.8                                | 9.4                             |
| 0.25         | 17.9                                | 9.1                             |
| 0.30         | 28.9                                | 8.5                             |
| 0.35         | 39.8                                | 8.0                             |
| 0.40         | 51.6                                | 7.4                             |
| 0.45         | 62.8                                | 6.7                             |

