| 1 out of 3                                                                    | Enter at least 3 more patients at this dose level. 
 
• If 0 of these 3 patients experience DLT, proceed to the next dose level.
 
• If 1 or more of this group suffer DLT, then dose escalation is stopped, and this dose is declared the maximally administered dose. Three (3) additional patients will be entered at the next lowest dose level if only 3 patients were treated previously at that dose.
 
 |
| $\leq 1$ out of 6 at highest dose level below the maximally administered dose | This is generally the recommended phase 2 dose. At least 6 patients must be entered at the recommended phase 2 dose.                                                                                                                                                                                                                                                                                                                                               |

The MTD is defined as the dose level immediately below the dose level at which  $\geq 2$  patients in a cohort (dose level) of 2 to 6 patients experienced a treatment-related DLT.

If MTDs are not determined at the dose of 2000 mg, this will be the dose taken to the expansion phase and no further escalation of dose is planned.

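### Protocol 13.1 both escalates and stops after 1 DLT in 6 patients, because its stopping sentence omits the limit that 5.4 places on it

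*Protocol*

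**What the plan says.** All references are to the Protocol. The following statements bear on what happens after 1 DLT in 6 patients.

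- **13.1, 3+3 paragraph, escalation sentence:** 1 DLT in 6 leads up one level. "If only 1 of the 6 patients experiences a DLT, then the next cohort of 3 patients will be treated at the next higher".
- **13.1, same paragraph, last sentence:** if 1 or fewer "in 6 patients experience DLT at a dose level, dose escalation will stop and this dose level will be the recommended dose". The dose meant is the one taken into expansion.
- **5.4, escalation table, row for 1 DLT in 3:** three more patients are entered. "If 0 of these 3 patients experience DLT, proceed to the next dose level".
- **5.4, escalation table, last row:** the rule that 1 or fewer DLTs identifies the recommended dose is limited to that count "out of 6 at highest dose level below the maximally administered dose".
- **5.4, MTD definition:** "The MTD is defined as the dose level immediately below the dose level at which" two or more patients have a DLT.
- **13.1, MTD definition, repeated in 13.3:** fewer than 2 of 6 with a DLT at the MTD, "with the next higher dose having at least 2 of 3 or 2 of up to 6 patients experiencing a DLT".
- **13.1, top dose:** "If MTDs are not determined at the dose of 2000 mg, this will be the dose taken to the expansion phase". Sections 1.4 and 5.4 say the same.

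**The concern.** A dose-escalation rule must give one instruction for each possible outcome. Here the outcome of 1 DLT in 6, reached after 1 DLT in the first 3, gets two: the next cohort goes up a level, or escalation ends and the current level goes to expansion.

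The last sentence of 13.1 also passes over the condition in every MTD definition that the next higher dose must have produced at least 2 DLTs. Identifying the MTD is a primary objective (1.1.2), and 13.1 enrolls 10 further patients at the dose selected. A team that followed the last sentence would stop with the next dose untested. It might carry forward a dose that is too low, and it would have no MTD as the protocol defines one. The mistake might also go unnoticed, because 13.1 allows expansion at the maximum administered dose when no MTD is determined.

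**Working it through.** The question is one of consistency; no figure stated in the protocol depends on it. The outcomes at one level run as 3+3 on the way up, below 2000 mg, are:

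| Outcome | 5.4 table | 13.1, escalation and toxicity sentences | 13.1, last sentence |
|---|---|---|---|
| 0/3 | escalate | escalate | does not apply (only 3 treated) |
| 1/3, then 0/3 (1/6 in total) | escalate | escalate | **stop; level goes to expansion** |
| 1/3, then 1 or more in the next 3 | stop; go to the level below | stop; go to the level below | does not apply |
| 2 or more in the first 3 | stop; go to the level below | stop; go to the level below | does not apply |

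The conflict is confined to the second row. The outcome 0/6 cannot arise on the way up, because 0/3 escalates at once. At a level filled to 6 after the level above proved too toxic, 1 or fewer in 6 raises no conflict: 5.4 and 13.1 agree.

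**Against the MTD definitions.** A level below 2000 mg that is stopped by the last sentence has no DLT data at the next higher dose. It therefore cannot satisfy the definition in 5.4 or the one in 13.1 and 13.3.

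**How often the conflict could arise.** Let p be the true DLT risk at a level. The protocol gives no DLT risk by dose, so every p below is an assumption.

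- P(1/6 on the way up) = P(1 of the first 3) × P(0 of the next 3) = 3p(1-p)^2 × (1-p)^3 = 3p(1-p)^5.
- P(escalate past the level), rule in 5.4 = (1-p)^3 + 3p(1-p)^5.
- P(escalate past the level), last sentence of 13.1 taken literally = (1-p)^3.

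| Assumed p | P(1/6 on the way up) | P(escalate), 5.4 | P(escalate), literal last sentence |
|---|---|---|---|
| 5% | 11.6% | 97.3% | 85.7% |
| 10% | 17.7% | 90.6% | 72.9% |
| 15% | 20.0% | 81.4% | 61.4% |
| 20% | 19.7% | 70.9% | 51.2% |
| 30% | 15.1% | 49.4% | 34.3% |

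Example at p = 10%: 3 × 0.10 × 0.90^5 = 0.30 × 0.590 = 0.177, and 0.90^3 = 0.729; the sum is 0.906.

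The derivative of 3p(1-p)^5 is 3(1-p)^4(1-6p), which is zero at p = 1/6. The maximum is 0.5 × (5/6)^5 = 0.201.

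**The case against.** The strongest reply is that context limits the sentence. It closes a sequence: 2 or more DLTs mark a level as too toxic, the level below is filled to 6, 6 patients are needed to declare an MTD, and then comes the rule for 1 or fewer in 6. Read in order, the level meant is the one just filled. Including 0/6 supports this, since 0/6 can arise at a filled level or at 2000 mg but not on the way up. Section 5.4 states the rule correctly, and the design is called a traditional 3+3 throughout.

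As an account of intent this is probably right, and the intended rule can be recovered from 5.4. The words of 13.1 still do not carry it. The sentence applies to a dose level without restriction. Saying that escalation will stop also fits poorly after de-escalation, when it has already stopped. No text says which section prevails, and the trial is multi-center.

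A second reply is that the sentence names an expansion dose, not an MTD, and that 13.1 permits expansion without an MTD. The distinction is fair: the direct contradiction is with the escalation rule. But 1.4, 5.4 and 13.1 tie the case without an MTD to 2000 mg, so stopping at 1/6 below that dose leaves the primary objective unmet.

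A third reply is that the probabilities do not measure harm. That stands. They give the chance that a level reaches the disputed outcome, not the chance that a team then applies the wrong sentence, for which there is no basis for an estimate. The literal reading is also the more cautious one for patients.

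**Conclusion.** The point holds. Section 13.1 is wrong as written: for 1 DLT in 6 on the way up it gives an instruction opposite to its own earlier sentence and to 5.4, and the resulting dose cannot meet the MTD definition unless it is 2000 mg. This conclusion rests on the text alone and needs no assumed DLT risk.

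As to size, the two sentences would conflict at no more than about one in five levels run as 3+3 (maximum 20.1%), and at 11.6% to 20.0% of such levels for the assumed risks tabulated. How many levels will run as 3+3 is unknown, because the trial starts with single-patient cohorts. No overdose risk follows; the harm would be escalation ended too early. Because the sentence selects the expansion dose and bears on a primary objective, it should be corrected before any level reaches 1/6.

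**What to change.** Replace the last sentence of the 3+3 paragraph in 13.1 with: *If 1 or fewer of 6 patients has a DLT at a dose level, and either the next higher level has already shown 2 or more DLTs or the level is 2000 mg, escalation stops and this level is the recommended dose for expansion. In all other cases, 1 DLT in 6 leads to the next higher level, as in Section 5.4.*

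This restores the limit in the 5.4 table, covers the top dose, and agrees with the MTD definitions in 5.4, 13.1 and 13.3. It costs one clause in an amendment and adds no patients, visits or procedures.

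### The expansion stopping rule in Section 13.1 is written for three differently defined events (DLT-criteria toxicities, SAEs and any adverse events), so what its boundary counts is not fixed

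*Protocol*

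**What the plan says.** All of the rule is in Protocol Section 13.1, and it applies to the expansion phase, in which "an additional 10 patients will be enrolled and treated at that dose level in an expansion phase".

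- **Rule sentence (DLT-criteria toxicity).** "If the rate of toxicities meeting DLT criteria appears to be higher than 30%, we will temporarily halt the study pending dose modification". The Bayesian version then "suspends the enrollment if the posterior probability of risk being larger than 0.3 is 75% or higher".
- **Expectation beside the prior (SAE).** "We expect the SAE rate is about 27" per cent. The Beta(2, 5.5) prior comes in the next sentence and is explained "as a prior distribution. This means that our prior guess at the proportion of toxicity is 27" per cent, adding that "there is 90% probability that this proportion is between 6% and 55" per cent.
- **Boundary table, examples and operating characteristics (AE).** The table row is labelled # AE, with stops at 2 of 2, 3 of 3–5, 4 of 6–8 and 5 of 9–10. The examples read "if two out of the first 2 patients have adverse events, we will stop the accrual" and "If three or more out of the first 3-5 patients have adverse events, we will stop". The operating characteristics are indexed by a true AE rate from 0.10 to 0.45.

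The protocol defines each term separately. Section 5.4 limits DLTs to listed toxicities at least possibly related to study drug, mostly grade 3 or higher non-hematologic or grade 4 hematologic, with exceptions. Section 7.1.2 defines SAEs by seriousness, with no relatedness condition. Section 7.1.1 counts as an AE any undesirable sign, symptom or condition after the start of study drug, related or not and with no minimum grade.

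**The concern.** A stopping boundary means something only for one defined event. Here the sentence stating the rule, the sentence motivating the prior, and the table and examples name three, and these occur at very different rates in patients with advanced cancer. The table and examples are the parts that convert directly into a decision after each patient, and both say adverse events without qualification. In a multi-center study, two people could follow the text faithfully and count different things.

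At stake is whether the rule does its job. Counting DLT-criteria toxicities, it is a reasonable guard against a risk above 30%. Counting every adverse event as Section 7.1.1 defines it, it would suspend enrollment at a dose that patients tolerate well. The SAE sentence also leaves unclear which event the 27% describes.

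**Working it through.** **Inputs from Section 13.1.** Prior Beta(2, 5.5); limit 0.3; posterior threshold 0.75; 10 expansion patients; boundary as printed. The any-AE rate is not in the protocol and is assumed over 0.50 to 0.95. (The 4.6% in Section 2.1 is the incidence of adverse drug reactions to IV mistletoe in an observational study, not an any-AE rate.) The comparison range of 0.10 to 0.167 for a DLT-type risk is also an assumption; its upper end is 1 in 6, the highest observed DLT proportion at which six patients still satisfy the MTD definition.

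**Step 1: reproduce the prior.** Mean = 2 / (2 + 5.5) = 26.7%. The 5th and 95th percentiles are 5.8% and 55.0%. Both match the text.

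**Step 2: reproduce the boundary.** After x events in n patients the posterior is Beta(2 + x, 5.5 + n − x). Stop when P(p > 0.3) ≥ 0.75.

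| Events / patients | P(p > 0.3) | Stop? |
|---|---|---|
| 2/2 | 0.769 | yes |
| 2/3 | 0.690 | no |
| 3/5 | 0.757 | yes |
| 3/6 | 0.689 | no |
| 4/8 | 0.752 | yes |
| 4/9 | 0.691 | no |
| 5/10 | 0.800 | yes |

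The minimum stopping counts for n = 2 to 10 are 2, 3, 3, 3, 4, 4, 4, 5, 5, identical to the printed table. The boundary is therefore correct for a single binary event with a 30% limit. What is unsettled is which event.

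**Step 3: reproduce the operating characteristics.** Exact recursion, one patient at a time, with the boundary checked after each patient up to n = 10.

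| True rate | Printed: % unsafe / mean n | Exact: % unsafe / mean n |
|---|---|---|
| 0.10 | 5.1 / 9.7 | 1.8 / 9.88 |
| 0.20 | 10.8 / 9.4 | 10.5 / 9.42 |
| 0.25 | 17.9 / 9.1 | 18.3 / 9.04 |
| 0.30 | 28.9 / 8.5 | 28.1 / 8.56 |
| 0.35 | 39.8 / 8.0 | 39.4 / 8.00 |
| 0.40 | 51.6 / 7.4 | 51.2 / 7.38 |
| 0.45 | 62.8 / 6.7 | 62.8 / 6.73 |

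Six rows agree within 1 percentage point. The 0.10 row does not. With 5000 simulations the standard error at 1.8% is √(0.018 × 0.982 / 5000) ≈ 0.19 points, so a gap of 3.3 points is not simulation noise. At a true rate of 0.15 the exact result is 5.1% and 9.70, which is the printed pair.

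**Step 4: apply the same boundary to different events.** The chance of stopping at patient 2 is p². A stop at exactly patient 3 is impossible, because 3 of 3 requires 2 of 2 first. The chance of stopping at patient 4 is 2p³(1 − p). At p = 0.90 these give 0.81 and 2 × 0.729 × 0.1 = 0.146. The recursion gives:

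| Event and true rate | % stopped | Mean n | % stopped by patient 3 |
|---|---|---|---|
| DLT-type, 0.10 | 1.8 | 9.9 | 1.0 |
| DLT-type, 0.167 | 6.7 | 9.6 | 2.8 |
| Any event at the stated 27% | 22.0 | 8.9 | 7.3 |
| Any AE, 0.50 (assumed) | 73.3 | 6.1 | 25 |
| Any AE, 0.70 (assumed) | 97.1 | 3.8 | 49 |
| Any AE, 0.80 (assumed) | 99.6 | 3.0 | 64 |
| Any AE, 0.90 (assumed) | 99.99 | 2.4 | 81 |
| Any AE, 0.95 (assumed) | >99.99 | 2.2 | 90 |

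**The case against.** The best defence is that the intended event can be worked out. The rule sentence names DLT-criteria toxicity, the Bayesian rule is introduced as its specification, the prior is described as a guess about toxicity, and a grid of rates from 0.10 to 0.45 would be an odd choice for any adverse event in this population. On that view AE is loose shorthand. This stands as evidence of intent, and the fix adopts it. It does not repair the text: AE is a defined term in the same protocol, the examples repeat it in words, and the SAE sentence introduces a third event that the shorthand reading does not explain.

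A reader might go further and infer that the expansion will almost surely close after two or three patients. The documents do not support that. It needs an any-AE rate that the protocol does not give. Even at assumed rates of 0.80, 0.90 and 0.95, stopping by patient 3 has probability 64%, 81% and 90%, all of it at patient 2. Near-certain eventual stopping is not the same as near-certain early stopping. The rule sentences also speak of a temporary halt or suspension, although the example speaks of stopping accrual.

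Nor do the printed operating characteristics become meaningless. They hold for any binary event at the tabulated rates, and the rows at 0.25 and 0.30 bracket the stated 27%. Finally, that the prior was derived from the SAE rate is an inference from adjacency and the shared 27%; the text itself calls it a guess about toxicity.

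**Conclusion.** The concern holds as an inconsistency in the definition of the monitored event. One rule uses three separately defined events, and its printed table and examples, followed literally, would suspend enrollment at a tolerable dose. The same boundary stops 1.8% to 6.7% of expansions for an event with true risk 0.10 to 0.167, but 73% at 0.50 and more than 99.9% at 0.90. The any-AE rates are assumptions, so the size of the effect depends on them, but its direction does not. Early closure is a hazard of the literal reading, not the evident plan.

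The prior, its interval and the boundary are internally correct. Of the operating characteristics, only the 0.10 row is wrong, and that error does not depend on which event is counted. Because the rule decides whether enrollment continues on safety grounds, the wording should be settled before the first expansion patient is enrolled.

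**What to change.** In Section 13.1, use the event that the rule sentence already names: patients with at least one toxicity meeting the Section 5.4 DLT criteria, one count per patient. Put it in the boundary-table label, both worked examples and the operating-characteristics label. Restate the 27% as the prior guess for that event, or drop the SAE sentence.

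In the same edit, correct the 0.10 row: either relabel it 0.15, which its printed values match, or keep 0.10 and print 1.8% and 9.9.

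Do not add a DLT-period window to the rule. Section 13.1 describes continuous evaluation throughout enrollment, so a window would be a new restriction. It would also rest on an unresolved conflict: Section 5.4 gives a DLT observation period of 28 days from first dose, and Section 13.1 gives the first three doses at the assigned level. Those two passages must be reconciled separately.

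The cost is a wording change in one section plus one table row. Boundaries, prior, threshold and sample size do not change.

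### The 0.10 row of the expansion-phase stopping-rule table is wrong: the printed rule gives 1.8% stopped and an average of 9.9 patients, not 5.1% and 9.7

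*Protocol*

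**What the plan says.** Section 13.1 (Study Design/Endpoints) describes the expansion phase and its safety monitoring.

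- **Size:** "an additional 10 patients will be enrolled and treated at that dose level in an expansion phase".
- **Looks:** "Continuous evaluation of toxicity events in the expansion cohort will be performed throughout enrollment".
- **Criterion:** the rule "suspends the enrollment if the posterior probability of risk being larger than 0.3 is 75% or higher". The prior is beta(2, 5.5).
- **Boundary:** stop at 2 events in 2 patients, 3 in 3 to 5, 4 in 6 to 8, or 5 in 9 to 10. The text illustrates the second of these: "If three or more out of the first 3-5 patients have adverse events, we will stop".
- **Performance:** a table introduced by "The operating characteristics of the stopping rule are shown below and are based on 5000 simulations". It has seven rows, for true rates 0.10, 0.20, 0.25, 0.30, 0.35, 0.40 and 0.45. The 0.10 row reads 5.1% declared unsafe and an average sample size of 9.7 out of 10.

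**The concern.** The spacing of the table is odd. From 0.20 upward the rows go in steps of 0.05, but the first step is 0.10 to 0.20. A 5.1% stopping probability at a rate of 0.10 also looks high for this boundary. The easiest way to stop is two events in the first two patients, and at a rate of 0.10 that has probability only 0.10 × 0.10 = 1%.

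The row matters because it is the lowest-toxicity scenario shown. It tells the reader how often enrollment would be suspended at a rate far below the 0.3 threshold. The table is also the only quantitative support that the protocol gives for this rule. A statistician who tries to reproduce it will fail on the first row and may then doubt the boundary, which is correct.

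**Working it through.** **Inputs, all from Protocol section 13.1:** prior beta(2, 5.5); stop when Pr(risk > 0.3 given the data) is at least 0.75; a look after each patient; at most 10 patients; 5000 simulated trials.

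**Step 1. Does the boundary follow from the prior and criterion?** After x events in n patients the posterior is beta(2 + x, 5.5 + n − x). Pr(risk > 0.3) is:

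- 2/2: 0.769 (stop)
- 3/5: 0.757 (stop); 3/6: 0.689 (continue)
- 4/8: 0.752 (stop); 4/9: 0.691 (continue)
- 5/10: 0.801 (stop); 4/10: 0.628 (continue)

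The full derived boundary is identical to the printed one, so the rule is unambiguous.

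**Step 2. Exact stopping probability.** Let p be the true rate and q = 1 − p. Some boundary points cannot be the first one hit; 3/3, for example, would already have stopped at 2/2. A first stop can occur only at patients 2, 4, 5, 7, 8 or 10. Counting the event sequences that reach each point without an earlier stop:

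| Stop at patient | Events | Sequences | Probability |
|---|---|---|---|
| 2 | 2 | 1 | p² |
| 4 | 3 | 2 | 2p³q |
| 5 | 3 | 5 | 5p³q² |
| 7 | 4 | 9 | 9p⁴q³ |
| 8 | 4 | 23 | 23p⁴q⁴ |
| 10 | 5 | 43 | 43p⁵q⁵ |

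P(stop) is the sum of the last column. The average sample size is 10 minus the sum of (10 − stopping patient) × probability:

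E[n] = 10 − 8p² − 6(2p³q) − 5(5p³q²) − 3(9p⁴q³) − 2(23p⁴q⁴)

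**Step 3. Reproduce a row that should be right, p = 0.30.** P(stop) = 0.0900 + 0.0378 + 0.0662 + 0.0250 + 0.0447 + 0.0176 = 0.2812, or 28.12%. The protocol prints 28.9%. The simulation standard error is √(0.2812 × 0.7188 / 5000) = 0.64 points, so the gap is 1.2 standard errors.

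**Step 4. The row in question, p = 0.10.**

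- P(stop) = 0.01000 + 0.00180 + 0.00405 + 0.00066 + 0.00151 + 0.00025 = 0.0183, or **1.83%**
- E[n] = 10 − 0.0800 − 0.0108 − 0.0203 − 0.0020 − 0.0030 = **9.88**
- Simulation standard error = √(0.0183 × 0.9817 / 5000) = 0.19 points
- Gap = 5.1 − 1.83 = 3.27 points, about 17 standard errors

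**Step 5. The missing grid value, p = 0.15.**

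- P(stop) = 0.02250 + 0.00574 + 0.01219 + 0.00280 + 0.00608 + 0.00145 = 0.0508, or **5.08%**
- E[n] = 10 − 0.1800 − 0.0344 − 0.0610 − 0.0084 − 0.0122 = **9.70**

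**Step 6. All rows together.**

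| True rate | Printed: % stopped, average n | Exact: % stopped, average n | Gap in % stopped, in simulation SE |
|---|---|---|---|
| 0.10 | 5.1, 9.7 | 1.83, 9.88 | +17 |
| 0.15 | not printed | 5.08, 9.70 | – |
| 0.20 | 10.8, 9.4 | 10.54, 9.42 | +0.6 |
| 0.25 | 17.9, 9.1 | 18.31, 9.04 | −0.8 |
| 0.30 | 28.9, 8.5 | 28.12, 8.56 | +1.2 |
| 0.35 | 39.8, 8.0 | 39.37, 8.00 | +0.6 |
| 0.40 | 51.6, 7.4 | 51.23, 7.38 | +0.5 |
| 0.45 | 62.8, 6.7 | 62.82, 6.73 | 0.0 |

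A separate simulation of 200,000 trials agrees: 1.81% and 9.89 at 0.10, and 5.05% and 9.71 at 0.15.

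**Step 7. Could another reading of the rule give 5.1% at 0.10?** The following were tried at a true rate of 0.10:

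- no look at patient 2: 1.1%
- no look at patient 10: 1.8%
- one final look at 5 or more of 10: 0.16%
- one final look at 4 or more of 10: 1.3%
- monitoring extended to 16 patients: 1.9%

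None comes near 5.1%. Solving in the other direction, the printed rule stops 5.1% of trials at a true rate of 0.1503.

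**The case against.** The arithmetic is hard to contest, but the weight of the error can be. The protocol expects a rate of about 27% and sets its threshold at 0.3. The rows nearest to those values (0.25 and 0.30) are correct, and the faulty row is the one furthest from the planning assumption. The 0.20 and 0.25 rows also describe rates below the threshold, so the 0.10 row is not the only evidence on false stops. The absolute gap is 3.3 percentage points and about 0.2 patients. It runs in the harmless direction, because it makes the rule look more prone to false stops than it is. The text also describes a trigger as a temporary halt, at least in one place, so a false stop need not end the phase. Nothing in the protocol says that any committee relies on this row. Finally, the 0.15 origin is an inference, since the document does not show whether the label or the values slipped.

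All of this stands as a limit on importance. None of it makes the row correct, and no other part of the protocol repairs it. That 5.1% and 9.7 are wrong for a true rate of 0.10 is a calculation and does not depend on how the error arose.

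**Conclusion.** The 0.10 row is wrong as written. Under the protocol's own rule the stopping probability at a true rate of 0.10 is 1.8%, not 5.1%, and the average sample size is 9.9, not 9.7. The printed false-stop risk is about 2.8 times the true one (5.1 / 1.83). The result assumes independent patients with a common event rate, a look after each patient, and a maximum of 10. The same assumptions reproduce the other six rows in both columns, which supports this reading of the rule.

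That the row really describes 0.15 is very likely, because both figures match and 0.15 is the missing step in the grid, but it is not proven. The error is confined to the description of the rule. It should be corrected, but it calls nothing in the design into question.

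**What to change.** In the operating-characteristics table of Protocol section 13.1, relabel the first row 0.15, keeping 5.1% and 9.7, and add a row for 0.10 with 1.8% declared unsafe and an average sample size of 9.9. The table is then correct whether the slip was in the label or in the values. If only one row is wanted, either relabel it 0.15 or keep 0.10 and print 1.8% and 9.9. Whoever holds the simulation output can confirm which slip occurred.

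The cost is a table correction. The prior, the criterion, the boundary, the sample size and the other six rows stay as they are.
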